### Setting

The study will be carried out in the field of healthcare and social work in nine municipalities in the Netherlands by the University of Twente and Arcon, an organization in the welfare sector. The study is funded by ZonMw (the Netherlands Organisation for Health Research and Development) under the prevention program. A municipal officer will generally be the local project leader, but in some cases, the local project leader works in one of the participating institutions. The local project leader is responsible for the recruitment through intermediaries, the allocation of participants to counselors and for the final approval on spending the budget in the Happiness Route. Municipalities mostly provide financial support for the training of counselors, the appointment of the local project leader, as well as the budget for the Happiness Routes. In other cases, the project is financed by social funds.

The recruitment of participants will be carried out by intermediaries who work as professionals in local care and social work institutions. Examples of intermediary organizations and professions are home care, housing associations, after-care nurses, psychiatric nurses, religious institutions, well-being institutions and organizations for people with mental disabilities. Intermediaries are in direct contact with the target group in their daily work. They can suggest possible candidates to the local project leader, who informed the intermediaries about the study and the target group.

Counselors are experienced professionals, such as social workers, and in some cases experienced volunteers. They are responsible for the intake and the delivery of the experimental and control interventions. To avoid contamination between the experimental and the control conditions, counselors will only deliver interventions in one of these conditions. Both counselors providing the Happiness Route and counselors providing the control condition will receive suitable training.

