### Randomization

When the written informed consent and the baseline questionnaire are received by regular mail, inclusion will be carried out on the basis of the criteria. Each included participant will be appointed randomly to either the intervention or the control condition, based on an a priori computer-generated randomized number list. No stratification will be carried out.

The principal investigator informs the local project leader of the outcomes of the inclusion and randomization procedure, so that the local project leader can appoint a counselor to deliver the intervention in the experimental condition (Happiness Route) or the control condition (Customized Care). It is not possible to blind the conditions to the counselors.

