#### Multivariate analyses

We will first do a missing data analysis for all participants on the second and third measurement point. A logistic regression analysis will be conducted with having complete data as the dependent variable, and demographic and psychosocial characteristics at baseline measurement as independent variables to assess non-random missings. We will use multiple imputations (five data sets) to replace missing values and carry out the analyses on the pooled data set. Hence, all participants who were randomized can be included in the statistical analyses. The results from this imputed intention-to-treat sample will be compared to the results of the observed data only.

We will use MANOVA analyses to assess the effectiveness of the intervention in reaching its primary and secondary outcomes. The measures at baseline, post-treatment, and follow-up are repeated measures and the experimental condition versus the control condition is the independent variable. In all analyses, we take into account that the observations are clustered as participants are ‘nested’ in each of the ten local institutions. Therefore, robust standard errors are computed using the first-order Taylor-series linearization method.

Standardized mean differences (Cohen's d) at post-intervention and follow-up are calculated as the difference between the means of the treatment and control condition divided by the standard error of the control condition. We expect a small to moderate effect size for the primary outcome (Cohen’s d= 0.35).

To answer the question on moderating participant factors, we will analyze the moderating effects of demographic characteristics (age, gender, and cultural background) on the effectiveness of the intervention. Following Kraemer et al.
[60], we will enter the change score of positive mental health at nine months minus baseline as a dependent variable in a linear regression model. The condition dummy (experimental versus control condition), the potential moderator, and their interaction are independent variables. When the interaction effect is significant, there is a differential effect of the intervention for this particular moderator. Analyses will be carried out for each of the three potential moderator variables separately.

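### MANOVA as named does not use the linearised standard errors that are meant to handle clustering, and its omnibus test has no direction although a one-tailed test is specified

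*Protocol article*

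**What the plan says.** All references are to the protocol article. Under Multivariate analyses: "We will use MANOVA analyses to assess the effectiveness of the intervention in reaching its primary and secondary outcomes". The layout follows: "The measures at baseline, post-treatment, and follow-up are repeated measures and the experimental condition versus the control condition is the independent variable". On clustering: "In all analyses, we take into account that the observations are clustered as participants are" nested "in each of the ten local institutions", and for that reason "robust standard errors are computed using the first-order Taylor-series linearization method". The same section plans five imputed data sets with pooled analysis.

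Other sections bear on this:

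- Randomization: "Each included participant will be appointed randomly to either the intervention or the control condition", and "No stratification will be carried out". Allocation is therefore by individual.
- Setting: the study runs "in nine municipalities in the Netherlands", which does not match the ten institutions of the analysis section or the ten communities of the abstract. Each counselor delivers only one of the two conditions.
- Power calculation and sample size: a one-tailed test at 0.05, d = 0.35, power 0.80.

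**The concern.** The paragraph joins two procedures without saying how they connect. The MANOVA criteria are computed from hypothesis and error cross-product matrices, with participants treated as independent. A robust standard error does not enter them, so computing one changes neither the statistic nor its p-value. To let the clustering reach the test, the analyst must form another statistic, with another reference distribution.

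The direction of the test raises a second problem. With three waves and two arms, the condition-by-wave hypothesis has two degrees of freedom. It can reject for any pattern of difference, including one against the Happiness Route. The sample size is built on a one-tailed comparison of two means, and the analysis section names no contrast or wave to which that comparison belongs.

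Several analyses with different error rates and different power therefore fit the text, and the choice among them could be made after the data are in.

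**Working it through.** **1. The plan's own sample size.** With d = 0.35, one-tailed alpha 0.05 and power 0.80, n = 2(1.645 + 0.842)² / 0.35² = 2 × 6.18 / 0.1225 = 100.9, so 101 per arm by the normal approximation. The exact t calculation gives 102 (power 0.801). Then 102 / 0.80 = 127.5, so 128 per arm and 256 in total. The stated figures reproduce. They belong to a single directional contrast and contain no clustering term.

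**2. What each statistic uses.** Let b be the two condition-by-wave contrasts.

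- Classical MANOVA (Hotelling form): T² = b′V⁻¹b, with V from the pooled residual cross-products of independent participants.
- Linearised version: W = b′V_r⁻¹b, with V_r = K/(K−1) times the summed cross-products of the centred cluster score totals, K being the number of institutions.

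Only W carries the stated adjustment. It can be referred to chi-square on 2 df, or to a small-sample F on 2 and K−2 df after scaling. These are different tests.

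**3. Clustering by site.** Simulation under no effect: 204 participants, 10 sites, individual 1:1 allocation, within-person correlation 0.5, nominal 0.05, 5,000 runs per setting. Site intraclass correlation (ICC) and effect variance are assumptions.

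- Constant effect, site ICC 0, 0.01, 0.05, 0.10: classical MANOVA 0.055, 0.052, 0.046, 0.047, essentially nominal.
- Effect varying between sites, independently at each wave, variance 0.01, 0.02, 0.05: classical MANOVA 0.064, 0.073, 0.107.
- Effect varying with SD 0.2, shared by both later waves (4,000 runs): classical MANOVA 0.075 with 204 participants and 0.080 with 256.
- W with the F reference stayed at 0.051-0.056 throughout. W with chi-square gave 0.129-0.139.

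Closed form for one contrast at SD 0.2 and 256 participants: variance 4/256 = 0.01563 becomes 0.01563 + 0.04/10 = 0.01963. The standard error ratio is 1.12, and P(Z > 1.645/1.12) = 0.071.

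**4. Clustering by counselor.** Counselors work in one arm only, so their effects do not cancel between arms. For one contrast, the design effect is 1 + (m−1)ICC and the true one-tailed error is P(Z > 1.645/√DE). Simulations used 256 participants, 10 sites and counselors nested in site and arm. The MANOVA column gives the results of two separate simulations.

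| Caseload m | ICC | DE | One contrast, closed form | Classical MANOVA, simulated |
|---|---|---|---|---|
| 5 | 0.05 | 1.20 | 0.067 | 0.065, 0.075 |
| 5 | 0.10 | 1.40 | 0.082 | 0.086, 0.094 |
| 8 | 0.05 | 1.35 | 0.078 | 0.097, 0.091 |
| 8 | 0.10 | 1.70 | 0.104 | 0.118, 0.117 |

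Across these settings W with the F reference gave 0.044-0.066, and W with chi-square 0.12-0.15. Institution-level linearisation absorbs counselor clustering provided each counselor works within one institution.

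**5. A single contrast, tested one-tailed.** In the settings of step 4, a contrast with the institution-linearised standard error and a t reference on 9 df had error 0.048-0.053. With a normal reference it had 0.064-0.070, in line with P(t₉ > 1.645) = 0.067.

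**6. Cost in power.** With 102 per arm and d = 0.35, the noncentrality is 0.35/√(4/204) = 2.50. One-tailed power is 0.80 with 202 df, 0.75 with 9 df (critical value 1.833 against 1.645) and 0.74 with 8 df (1.860). For the two-df omnibus test, simulation gave about 0.73 for classical MANOVA and 0.56-0.57 for W with F.

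**The case against.** The strongest reply is that the paragraph should be read as a whole: a multivariate repeated-measures model with cluster-robust inference. The MANOVA hypothesis is a linear hypothesis on coefficients. Those coefficients have a covariance matrix, which can be linearised and tested by a Wald or F statistic, as step 2 shows. The text says outright that clustering is taken into account, and a condensed article may leave the exact statistic to its analysis plan. For the clusters the plan names, individual randomisation makes the harm of ignoring them negligible unless the effect differs between sites. The caseloads and counselor ICC are not in the document.

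Most of this stands. A reader might infer that the two instructions cannot both be followed, or that the primary test ignores clustering. The document supports neither: a feasible test joins the two, and the intention to adjust is explicit. Nor does MANOVA rule out pooling after imputation, because multi-parameter combination rules exist. They do, however, need estimates and a covariance matrix rather than the MANOVA criteria themselves.

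Two things survive. The test that is named does not take up the adjustment that is named, and the statistics that would do so differ widely in error rate. The mismatch between an omnibus test and a one-tailed specification is also in the published text. It is not a detail deferred elsewhere.

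**Conclusion.** The point holds as a mismatch between the named test and two other stated features: the clustering adjustment and the one-tailed specification. It does not show that the plan omits clustering.

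If classical MANOVA were run, type I error at nominal 5% would stay near 5% with a site effect common to both arms. It would be about 7-8% with a between-site effect SD of 0.2 shared across waves, and higher if the variation were independent by wave (10.7% at variance 0.05, an SD of about 0.22). It would be about 7-12% with counselor caseloads of 5-8 and ICC 0.05-0.10. All these inputs are assumptions, and the result depends on them.

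The reference distribution matters as much as the label. With about ten clusters, an uncorrected chi-square version of the linearised test has an error of 12-15%, worse than the unadjusted MANOVA in the same settings. This should be settled in the plan before outcome data are seen.

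**What to change.** For the primary outcome, replace MANOVA with a linear model for the repeated scores containing condition, wave and condition-by-wave terms, fitted in each imputed data set. Then state:

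- one primary condition contrast and the wave at which it is evaluated, since the document names neither;
- a one-tailed test of that contrast using the institution-level linearised standard error;
- a small-sample t (or F) reference with degrees of freedom based on the number of institutions, not a normal or chi-square reference;
- pooling of that contrast and its variance across the imputed sets.

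Reconcile nine municipalities with ten institutions, because that count sets the degrees of freedom.

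The cost is wording and no new data. The critical value rises from 1.645 to 1.833 with ten institutions, about 11%, or to 1.860 with nine, about 13%. At the planned 102 evaluable per arm, power falls from 0.80 to about 0.75 or 0.74. That is a smaller loss than keeping the omnibus hypothesis with the same correction (0.56-0.57).

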### Power calculation and sample size

Based on a meta-analysis of previous studies in positive psychology, conducted with instruments that are similar to the MHC-SF
[27], we expect a small to medium effect size for the intervention Happiness Route (Cohen’s d = 0.35). A pilot study
[25] and experiences from previous practice showed that there are no negative effects on the well-being of participants. We therefore specified a one-tailed test with an alpha level of 0.05 under the assumption that the Happiness Route will be more effective than the Customized Care group, as the latter is not intended to improve positive mental health. This has also been shown in previous studies on positive psychological interventions
[27]. Given ethical considerations, Knottnerus and Bouter
[61] argued that one-sided testing is preferable under these circumstances. Power analysis with the program GPower with a power of 0.80 (1 – beta of 0.20), indicates that 102 participants are needed in each condition. We used a maximal drop-out rate of 20% which is a conservative estimate from previous experience. In everyday practice, the drop-out was about 10% of the more than 500 people who already participated in a Happiness Route. With a maximal drop-out of 20%, we need 128 participants in each condition, 256 in total.

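### Cohen's d is defined with the control condition's standard error instead of its standard deviation; applied literally, this would inflate the reported effect sizes several-fold

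*Protocol article*

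**What the plan says.** The definition stands in the protocol article, Statistical analyses, under Multivariate analyses. Standardized mean differences, labelled Cohen's d, are to be given at the two post-baseline measurements and are "calculated as the difference between the means of the treatment and control condition divided by the standard error of the control condition". The next sentence reads "We expect a small to moderate effect size for the primary outcome" and gives the value 0.35.

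The section Power calculation and sample size uses the same figure: "we expect a small to medium effect size for the intervention Happiness Route", again with d = 0.35, drawn from a meta-analysis. It continues "We therefore specified a one-tailed test with an alpha level of 0.05", then "Power analysis with the program GPower with a power of 0.80", which "indicates that 102 participants are needed in each condition". After a drop-out allowance of 20%, the target is 128 per arm and 256 in total.

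Two other statements under Multivariate analyses bear on the point. Standard errors are to be made robust to clustering within local institutions by Taylor linearization. Results from the multiply imputed sample of all randomized participants are to be compared with results from the observed data alone. The article nowhere gives the denominator of d as a standard deviation.

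**The concern.** A standardized mean difference expresses the gap between two means in units of the spread between individuals, so its denominator is an SD. A standard error describes the precision of a mean. Dividing by it gives a number that grows with the square root of the sample size even when the effect does not change.

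Three things are at stake if the sentence is followed:

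- The reported values would be far too large to read as Cohen's d.
- They could not be set beside the protocol's 0.35, or beside the literature from which that figure was taken.
- The same mean difference and SD would give different values when the number of controls differs, as in the planned comparison of imputed and observed data.

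This is a stated formula, not a detail left open, so a separate analysis plan would have to contradict the article in order to correct it.

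**Working it through.** **Inputs.** d = 0.35 (Multivariate analyses; Power calculation and sample size). One-sided alpha 0.05, power 0.80, 102 evaluable per arm, 20% drop-out and 128 randomized per arm (all from Power calculation and sample size). The denominator is the control condition's standard error (Multivariate analyses).

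**Step 1: reproduce the plan's own figure with d in SD units.**

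- Normal approximation: n per arm = 2(1.645 + 0.842)²/0.35² = 12.37/0.1225 = 100.9, so 101.
- Exact calculation with the noncentral t distribution: power is 0.798 at 101 per arm and 0.801 at 102. The smallest n that reaches 0.80 is 102, as stated.
- Drop-out: 102/0.80 = 127.5, so 128 per arm, as stated.

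The 0.35 used for planning is therefore a difference divided by an SD.

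**Step 2: test the alternative, that 0.35 is on the written scale.**

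- With SE = SD/sqrt(n), the difference in SD units would be 0.35/sqrt(102) = 0.035 or 0.35/sqrt(128) = 0.031.
- Power at those sizes would be about 8%, and 80% power would need about 10,300 to 12,900 per arm.

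The written definition and the stated sample size cannot both apply to the same d.

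**Step 3: inflation with a simple standard error.**

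With SE = SD/sqrt(n), difference/SE = (difference/SD) × sqrt(n), where n is the number of controls.

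| Controls | Factor sqrt(n) | True 0.35 reported as |
|---|---|---|
| 102 | 10.1 | 3.53 |
| 128 | 11.3 | 3.96 |

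**Step 4: inflation with a cluster-robust standard error.**

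The factor becomes sqrt(n/design effect). The article gives no design effect; the range 1 to 2 is an assumption.

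| Controls | Design effect 1 | Design effect 2 |
|---|---|---|
| 102 | 10.1 | 7.1 |
| 128 | 11.3 | 8.0 |

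**Step 5: dependence on the number analysed.**

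Suppose 128 controls in the imputed sample, 102 in the observed data, the same mean difference and SD, and a simple standard error. The two values would differ by a factor of 11.3/10.1 = 1.12, that is 12%, from the count alone. A standard error that also carries imputation uncertainty would change this figure. The general dependence on n would remain.

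**The case against.** The strongest reply is that this is a one-word slip. The same sentence calls the quantity Cohen's d, the next one expects a small to moderate 0.35, and the sample size works only in SD units. An analyst who obtained 3.5 would probably notice. That is a fair account of how the error arose, and a reader should not infer that the published effect sizes will in fact be ten times too large. The article shows only what literal use would give. The reply does not remove the need for a correction: the sentence is the article's only definition of the effect size, and the same section has the analyst computing standard errors.

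A second reply is that nothing inferential depends on the definition. This stands. Effectiveness is judged by MANOVA with robust standard errors, moderators are examined by regression on change scores, and the power calculation uses d correctly. The article also sets no rule that compares the observed d with 0.35; that figure is an expectation and a planning input.

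A third reply is that a factor of exactly sqrt(n) presumes a simple standard error, whereas the plan accounts for clustering and uses imputation. This also stands, and the size is therefore given as conditional.

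Finally, a reader might infer that unequal response between the two arms would put them on different scales. It would not: only the control condition enters the denominator, and each d is a single between-arm number. In the imputed sample the nominal number of controls is also the same at both time points, so dependence on responder counts concerns mainly the observed data.

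**Conclusion.** The definition is wrong as written and is inconsistent with the protocol's own use of d = 0.35, which reproduces 102 per arm only in SD units.

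Applied literally with a standard error of SD/sqrt(n), it would inflate the reported effect sizes about 10.1-fold at 102 controls and 11.3-fold at 128, so that a true 0.35 would appear as about 3.5 to 4.0. With a cluster-robust standard error, and an assumed design effect of 1 to 2, the factor would be about 7.1 to 11.3. Any such value would also vary with the number of controls analysed.

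The consequence is confined to the reported effect sizes. The documents do not support extending it to the tests, the sample size or the moderator analyses.

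**What to change.** Under Multivariate analyses, replace the standard error of the control condition with the standard deviation of the control condition as the denominator of Cohen's d. The rest of the sentence can stay.

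The control condition should be kept as the reference. A pooled baseline SD would be a poorer choice here, because eligibility cuts off the range of several outcomes at baseline: MHC-SF scores of 4.83 or higher are excluded, a loneliness score of at least 3 is required, and a CES-D score of 39 or higher is the cut-off for excluding serious untreated depression. An SD narrowed in this way would tend to enlarge d. Adding a confidence interval or a baseline-adjusted difference is a matter of preference and is not needed to correct this error.

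The change costs one phrase. It needs no further data or participants and alters no planned test.

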### Measures

#### Data collection

An overview of the measures can be seen in Table 
1. Participants have to complete paper and pencil questionnaires during the intake (baseline), after the end of the intervention (three months after the baseline), and nine months after the intake (follow up). All outcome measures will be recorded at all three measurements. Demographic variables will be filled out only at baseline. The baseline questionnaire will be filled out during the intake. Participants fill it out by themselves, but can ask the counselor when help is needed. The second and third questionnaires will be sent by regular mail to participants, accompanied by reply-paid envelopes. If participants need help with filling in the questionnaire, their counselor can help them. Otherwise, the counselor is not involved in the second and third measurement. An overview of the measures can be seen in Table 
1.

**Table 1 T1:** Study parameters and measurement instruments

**Outcome measure**	**Instrument**

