We do similar regression analyses to answer the question on moderating counselor factors. The potential moderators are the indices for work experience, work satisfaction, and adherence to the program as measured with the questionnaire for counselors and the logs of the counselors.

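### The moderator regressions analyse raw MHC-SF change without baseline MHC-SF as a covariate, which loses precision in interaction tests that are already weak

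*Protocol article*

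**What the plan says.** The Multivariate analyses section of the protocol article fixes the outcome of the participant moderator models: "we will enter the change score of positive mental health at nine months minus baseline as a dependent variable in a linear regression model". It then lists the predictors: "The condition dummy (experimental versus control condition), the potential moderator, and their interaction are independent variables". There is one model each for age, gender and cultural background: "Analyses will be carried out for each of the three potential moderator variables separately". A significant interaction is the stated criterion for a differential effect. For the counselor indices (work experience, work satisfaction, adherence) the article says "We do similar regression analyses to answer the question on moderating counselor factors".

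No section adds baseline MHC-SF to these models. The only general addition to all analyses is robust standard errors for clustering by local institution.

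The baseline score is available. Under Data collection: "All outcome measures will be recorded at all three measurements". Under Randomization, inclusion is decided once the baseline questionnaire has been returned, and under Participants an MHC-SF score of 4.83 or higher excludes a candidate.

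The Background and the Discussion both say that no moderation is expected, and the Discussion presents these analyses as the test of that expectation.

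**The concern.** Using raw change as the outcome forces the slope of the nine-month score on baseline to be 1. If the true slope is below 1, part of the baseline variation stays in the residual and widens the standard error of the interaction. A baseline covariate would remove it at almost no cost.

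This matters because the investigators expect the null result and the decision rule is significance. Avoidable noise makes that expected answer more likely whether or not it is true. The point concerns only the moderator regressions. The repeated-measures MANOVA for the main comparison is a different model and is not affected.

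**Working it through.** **The plan's own figure.** The sample size covers the main effect only: "We therefore specified a one-tailed test with an alpha level of 0.05", power 0.80, d = 0.35. The normal approximation gives 2 × (1.645 + 0.842)² / 0.35² = 100.9, so 101 per arm. The exact noncentral t calculation gives 102 per arm (power 0.801). With 20% drop-out, 102 / 0.80 = 127.5, so 128 per arm and 256 in total. The stated figures reproduce and are not in dispute. No power is given for the moderator tests.

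**Residual variance.** Let b be the slope of the nine-month score on baseline.

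- Change-score residual variance = adjusted residual variance + (1 − b)² × Var(baseline).
- The excess is zero only if b = 1. Otherwise the adjusted model is more precise, apart from one degree of freedom.
- With SD 1 at both times, b = rho. The adjusted variance is 1 − rho², and the change-score variance is (1 − rho²) + (1 − rho)² = 2(1 − rho). The ratio of adjusted to change-score variance is (1 + rho)/2.

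**Inputs for power.** From the document: 102 completers per arm, so N = 204, with 1:1 allocation. Assumed, because the document gives none of them for these tests: rho; a two-level participant moderator split 50/50; an interaction of 0.35 SD, as large as the whole expected main effect; a two-sided 0.05 test; no clustering.

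The interaction is a difference of differences over four cells of N/4, so its variance is 16v/N and its SE is 4√v/√204 = 0.280√v. Power is approximately Φ(0.35/SE − 1.96).

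| rho | v, change score | v, adjusted | SE, change score | SE, adjusted | Power, change score | Power, adjusted |
|---|---|---|---|---|---|---|
| 0.3 | 1.40 | 0.91 | 0.331 | 0.267 | 18% | 26% |
| 0.5 | 1.00 | 0.75 | 0.280 | 0.243 | 24% | 30% |
| 0.7 | 0.60 | 0.51 | 0.217 | 0.200 | 36% | 42% |

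At rho 0.5 the interaction detectable with 80% power is (1.96 + 0.842) × SE: about 0.78 SD with the change score and 0.68 SD with adjustment. The change-score model would need 204 / 0.75 = 272 completers to match the adjusted model's precision.

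**Check by simulation.** With 2000 simulated trials at N = 204 and rho 0.5, power was 24.4% and 31.8%, and the empirical SE 0.278 and 0.241. The mean interaction estimates were 0.360 and 0.359 against a true 0.35, so neither model is biased. With baseline in the model, change and the nine-month score gave the same interaction estimate.

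**Effect of the eligibility cut-off.** Excluding high MHC-SF scores leaves b unchanged but can shrink Var(baseline), and with it the gain. As an illustration, assume a normal baseline cut at +1 SD and rho 0.5. The remaining variance is 1 − 0.288 − 0.288² = 0.63. The change-score residual variance is then 0.75 + 0.25 × 0.63 = 0.907, and adjustment removes 0.157 / 0.907 = 17% of it, compared with 25% under equal SDs. If the recruited population mostly scores well below the cut-off, the figure moves back towards 25%.

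**The case against.** The strongest reply is that the planned model is valid. Arms are randomized, so within each level of a participant characteristic the baseline is balanced in expectation, and the change-score interaction is unbiased. The model is prespecified, follows a cited moderator framework and concerns a secondary question. The gain is a few percentage points of power, and the tests are weak with or without it.

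Most of this stands, and it limits the point to precision. It does not justify leaving out a covariate that is already collected, since the condition, moderator and interaction terms of the framework stay as they are.

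A reader might infer more than the document supports:

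- **Regression to the mean distorts the moderator findings.** The plan bases its conclusion on the interaction and does not interpret moderator main effects. Nor must a group that starts lower show a larger change, because stable groups regress towards their own means.
- **The power figures can be raised to the full 256.** That would treat imputed nine-month scores as if they had been observed.
- **The power figures cover all six moderators.** They describe a balanced two-level participant trait. Age is naturally continuous. The counselor indices belong to counselors who each work in one condition and are appointed after allocation, and adherence arises during delivery. Neither the power figures nor the argument from randomization carries over to those models. That they omit baseline at all is inferred from their being described as similar.

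**Conclusion.** The point holds as a modest, avoidable loss of precision in secondary analyses. The participant moderator model is explicit and omits baseline MHC-SF; the counselor models follow by description. The direction of the loss does not depend on the assumptions, unless the slope on baseline is exactly 1. Its size does. Under the stated assumptions, power at 204 completers rises by about 5 to 8 percentage points for rho between 0.7 and 0.3, and by less if the MHC-SF cut-off narrows the baseline variance. Uneven splits, such as are likely for cultural background, and clustering would lower power under either model.

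A reader might conclude that adjustment makes these tests adequate. It does not: at rho 0.5 power is still only about 30% for an interaction as large as the whole expected treatment effect. Under either model, a non-significant interaction is weak evidence for the expectation of no moderation.

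**What to change.** In the Multivariate analyses section, add baseline MHC-SF as a covariate beside condition, moderator and interaction in each participant moderator model, and state the same for the counselor models. The change score may stay as the outcome if comparability with the cited framework is wanted, because with baseline included it gives the same interaction estimate as the nine-month score.

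Report each interaction with its confidence interval, and state that a non-significant result will not be taken as confirming the absence of moderation.

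The cost is a few words of analysis text and one degree of freedom per model. No new data are needed and the sample size is unchanged.
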